### Study aims and hypotheses

1.1

The primary objective of this RCT is to evaluate the immediate efficacy of the SAF-T intervention in alleviating psychological distress (a composite of stress, anxiety, and depressive symptoms) among family members of ICU patients, as measured on Day 3 post-enrollment (immediately after intervention completion). Secondary objectives include: (1) To assess the longitudinal trajectories of stress, anxiety, and depressive symptoms in family members receiving the SAF-T intervention, examining its sustained effects at Day 3 post-enrollment (post-intervention), upon patient transfer from the ICU, and at the Day 30 and Day 90 follow-ups. (2) To explore the potential of the SAF-T intervention for preventing PTSD symptoms, measured at Day 3 post-enrollment (post-intervention), upon patient transfer from the ICU, and at the Day 30 and Day 90 follow-ups. (3) To explore the effect of the SAF-T intervention on sleep quality, measured at Day 3 post-enrollment (post-intervention), upon patient transfer from the ICU, and at the Day 30 and Day 30 follow-ups.

Based on the objectives above, the following hypotheses are proposed: (1) Primary Hypothesis: Compared to family members receiving usual care (control group), those receiving the SAF-T intervention will demonstrate a significantly lower composite score of psychological distress after completing the 3-day intervention period (Day 3 post-enrollment). (2) Secondary Hypotheses: (1) Compared to the control group, the intervention group will show greater reductions or faster improvement in individual scores on the perceived stress scale (PSS-10), generalized anxiety disorder scale (GAD-7), and patient health questionnaire (PHQ-9) from baseline to each follow-up assessment. (2) Compared to the control group, the intervention group will have significantly lower impact of event scale-revised (IES-R) scores (indicating fewer PTSD symptoms). (3) Compared to the control group, the intervention group will have significantly lower sleep quality index (PSQI) scores.

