Analysis of Secondary and Longitudinal Outcomes: For longitudinal analyses of secondary outcomes—including the individual trajectories of PSS-10, GAD-7, and PHQ-9 scores, as well as PSQI and IES-R scores across time points (Day 3, discharge, Day 30, Day 90)—linear mixed-effects models (LMMs) will be employed. This approach handles missing data under the missing-at-random (MAR) assumption and accounts for within-subject correlation. Separate LMMs will be fitted for each continuous secondary outcome. Each model will include: (1) Fixed Effects: Treatment group, time (as a categorical factor), the group × time interaction, and the corresponding baseline score of the outcome as a covariate. (2) Random Effects: A random intercept for each participant will be included to account for individual variability. (3) Covariance Structure: An unstructured covariance matrix will be initially specified to model the within-subject errors, with the final structure chosen based on model fit indices (e.g., Akaike Information Criterion). The group × time interaction will be the effect of primary interest, testing whether the change in the outcome over time differs between groups. If the interaction is significant, simple effects analyses (e.g., between-group comparisons at each time point) will be conducted. For the primary ITT analysis, missing outcome data at Day 3 will be handled using the Multiple Imputation (MI) method. Results from analyses on each dataset will be pooled using Rubin’s rules. For longitudinal LMMs, the full-information maximum likelihood (FIML) estimation inherent to the method will be utilized.

Handling of Multiplicity: All analyses of secondary outcomes and longitudinal trajectories are considered exploratory. Results from these analyses will be presented with point estimates and 95% confidence intervals to indicate the magnitude and precision of effects. *p*-values from these exploratory analyses will be interpreted descriptively and with caution, without formal adjustment for multiple testing, to avoid inflating Type II error rates while generating hypotheses for future research.

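### Each secondary mixed model uses one baseline slope for all visits from Day 3 to Day 90; a baseline × time term would be a cheap gain in precision if that slope weakens over time

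*Protocol article*

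**What the plan says.** Section 2.6 (Analysis of Secondary and Longitudinal Outcomes) fits a separate linear mixed model to PSS-10, GAD-7, PHQ-9, IES-R and PSQI at four post-baseline visits: Day 3, ICU discharge, Day 30 and Day 90.

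- **Fixed effects:** group, categorical time, "the group × time interaction, and the corresponding baseline score of the outcome as a covariate". No baseline × time term is listed.
- **Random effects:** "A random intercept for each participant will be included to account for individual variability".
- **Residual covariance:** "An unstructured covariance matrix will be initially specified to model the within-subject errors", with the final structure chosen by fit indices such as AIC.
- **Target:** the group × time interaction is the effect of primary interest, and between-group comparisons at single visits follow only if it is significant.

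For stress, anxiety and depression, these models serve the objective in section 1.1 of "examining its sustained effects at Day 3 post-enrollment (post-intervention), upon patient transfer from the ICU, and at the Day 30 and Day 90 follow-ups". The protocol also states: "All analyses of secondary outcomes and longitudinal trajectories are considered exploratory".

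**The concern.** A baseline main effect without a time interaction assumes that a Day 1 score predicts Day 90 with the same slope as it predicts Day 3. Baseline is measured during an acute ICU crisis, so a weaker slope at Day 90 is plausible. A single slope is then a compromise, too shallow for Day 3 and too steep for Day 90. A chance baseline difference between two arms of 28 is corrected with the wrong weight at both ends.

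The interaction is affected too. A slope shared by all visits drops out of any difference between visits, so the contrast that the plan singles out gains nothing from the covariate. The late visits, which answer the sustained-effect question, would be estimated less precisely than the data allow.

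**Working it through.** **Inputs from the protocol.** There are 28 per group: the stated 22 reproduces for a two-sided t-test with d = 1.13, alpha 0.05 and power 0.95, and 22/0.8 = 27.5, rounded up to 28. The mean model and visits are as above.

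**Assumed inputs.** The protocol gives no correlations. I take SD 1 at every visit, complete data, baseline correlations ρ falling from 0.6–0.8 at Day 3 to 0.2–0.3 at Day 90, and correlation between adjacent visits of 0.6–0.7 that decays with distance (matrix R).

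**Step 1: the estimate.** With group × time saturated and complete data, the group effect at visit t under a common slope β is

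ΔY(t) − β·Δb,

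where Δ is the difference in arm means and b is baseline. Subtracting two visits gives ΔY(90) − ΔY(3). The baseline term has gone, whatever the covariance structure.

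**Step 2: the common slope.** Under unstructured covariance, β = 1′S⁻¹ρ / 1′S⁻¹1 with S = R − ρρ′. Under compound symmetry, β is the plain mean of the visit slopes.

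**Step 3: variance ratios, common slope against visit-specific slopes.** These are before the 1–2% that the extra parameters cost.

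- Single visit: 1 + (ρ(t) − β)² / (1 − ρ(t)²)
- Day 90 minus Day 3: v / (v − (ρ(90) − ρ(3))²), with v = 2(1 − r) and r the correlation between Day 3 and Day 90.

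*Case A: ρ = 0.7/0.6/0.4/0.3, adjacent correlation 0.7, so r = 0.7³ = 0.343 and v = 1.314.*
- Unstructured: simulated β = 0.576. Day 90: 1 + 0.276²/0.91 = 1.084. Day 3: 1 + 0.124²/0.51 = 1.030.
- Compound symmetry: β = 2.0/4 = 0.50. Day 90: 1 + 0.20²/0.91 = 1.044.
- Contrast: 1.314/(1.314 − 0.16) = 1.139.
- Simulation check (1,500 trials, unstructured): Day 90 SD ratio 1.0432, squared 1.088; mean bias about 0.

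*Shallow end: ρ = 0.6/0.5/0.4/0.3.*
- Compound symmetry: β = 0.45. Day 90: 1 + 0.15²/0.91 = 1.025, about 1% net of the parameter cost.
- Contrast with adjacent correlation 0.6: r = 0.216, v = 1.568, and 1.568/(1.568 − 0.09) = 1.061, about 4% net.

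*Steeper: ρ = 0.7/0.5/0.3/0.2, adjacent correlation 0.7.*
- Unstructured: β = 0.549. Day 90: 1 + 0.349²/0.96 = 1.127.
- Contrast: 1.314/(1.314 − 0.25) = 1.235.

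*Constant ρ = 0.5.* There is no loss. The simulated SD ratio is 0.9944, squared 0.989, so baseline × time costs about 1%.

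**Beyond that range.** The 4–23% for the contrast corresponds to falls in correlation of 0.3 to 0.5. A fall of 0.6 (0.8 to 0.2) gives 1.314/(1.314 − 0.36) = 1.377. With ρ = 0.7/0.5/0.3/0.2 but all visits equally correlated at 0.55, the simulated Day 90 SD ratio was 1.1044, squared 1.22.

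**Step 4: chance imbalance.** One standard error of the baseline difference is √(2/28) = 0.267 SD. With a Day 90 slope error of 0.2 to 0.4, the Day 90 estimate moves by 0.267 × 0.2 = 0.05 to 0.267 × 0.4 = 0.11 SD. The direction follows the chance imbalance.

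**The case against.** The strongest reply is that this is a valid model for a randomised trial. With complete data the simulations show mean bias of about zero and type I error of about 5–6%, whether or not the slope changes. The harm rests wholly on assumed correlations, and a constant slope removes it. A Day 90 shift of 0.05–0.11 SD is small beside a Day 90 standard error of about 0.27 SD. The outcomes are exploratory, and a baseline × time term might be left to an analysis plan that is not shown.

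Most of this stands and limits the point to a suggested improvement. The last part does not: the article lists the fixed effects explicitly, so this is a stated model. Choosing the covariance by AIC alters the value of the common slope but does not give each visit its own.

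A reader might infer that the Day 90 group difference is biased. The documents do not support that. Under randomisation with complete data, the error averages to zero. In simulations where dropout depended on baseline in opposite directions by arm, the common slope gave a Day 90 bias of 0.10–0.20 SD and type I error up to 9.1%, against 0.01 SD and 5.1% with visit-specific slopes. But section 3.1 names attrition as a risk, not attrition that differs by arm in this way.

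**Conclusion.** The point holds as a matter of efficiency. The secondary models impose one baseline slope on four visits spanning about 90 days, and with complete data this leaves the group × time contrast without baseline adjustment. The cancellation is algebra; with missing visits it is no longer exact.

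Its cost depends on the assumed decline in correlation: about 1–13% more variance at Day 90, depending on the covariance structure, and about 4–23% more for the Day 90 minus Day 3 group contrast. It is larger for the steepest declines or for flat between-visit correlation, and nil for a constant slope. No systematic error in the treatment effect is shown. The primary Day 3 comparison is a single-visit ANCOVA and is untouched. This is a worthwhile minor improvement, and no conclusion of the trial hangs on it.

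**What to change.** Add baseline × time (categorical) to the fixed effects of each secondary model, so that every visit has its own baseline slope. From that model, report the baseline-adjusted group difference with its 95% CI at each visit. Make the change before unblinding.

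It takes three further parameters per model and no new data. If the slopes are in fact equal, it costs about 1–2% in variance.

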**Methods:**

This study will recruit 56 family members of ICU patients from a hospital in China. Participants will be randomly assigned to either the experimental group or the control group. The control group will receive standard care, and the experimental group will receive standard care plus a stress management intervention. The primary outcome is a composite score of psychological distress (integrating perceived stress, anxiety, and depression) measured immediately post-intervention. Secondary outcomes include the longitudinal trajectories of individual psychological symptoms (stress, anxiety, depression), symptoms of post-traumatic stress, and sleep quality across multiple follow-ups up to 90 days. Data analysis will be performed utilizing IBM SPSS version 27.0 software.

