#### Sample size

2.1.2

The sample size estimation for this study was calculated based on the results of a pilot study by Cairns (2018). This pilot study was selected as a reference for several reasons: both studies involve similar populations (family members of ICU patients), comparable intervention intensity (continuous intervention over 3 days, each lasting 15–20 min), similar assessment tools and outcome indicators (key indicators in this study were selected from those that performed well in the Cairns’ study, or alternative validated tools were chosen to address its limitations), and largely aligned assessment time points (the Cairns’ study assessed on Day 1, Day 3, Day 30, and Day 90; this study additionally included an assessment within 24 h after patient discharge to better reflect the interaction between patients and their families). In the pilot study (*N* = 10; 5 per group), the effect size for the outcome of perceived stress from baseline to 90-day follow-up was Cohen’s *d* = 1.13 (95% CI: −0.21 to 2.47), based on a mean difference of 4.4 points (intervention: 23.0 ± 2.30 vs. control: 25.0 ± 5.05). This effect size represented the most conservative estimate among all follow-up time points (Day 3: *d* = 1.50; Day 30: *d* = 1.23; Day 90: *d* = 1.13). Sample size estimation for the “independent sample *t*-test” was performed in G Power3.1 sample size calculation software,^1^ and the calculation formula is as follows: 
$n={\left[\frac{Z_{\alpha /2}+Z_{\beta }}{\delta /\sigma }\right]}^{2}(Q_{1}^{-1}+Q_{2}^{-1})$
 (Faul et al., 2007; Faul et al., 2009). The parameter Settings are as follows: For the two-sided test, Cohen’s d is 1.13, Alpha is 0.05, the certainty Power (1-β) is 0.95, and the sample size is selected as N1 = N2. Finally, it was calculated that each group of the intervention study required 22 people. Considering a loss to follow-up rate of more than 20%, the minimum sample size included in each group was ultimately 28 people. When the sample size was sufficient, as many research subjects as possible were included in the study. Acknowledging the inherent variability and potential overestimation in pilot studies, we aimed for a conservative design by selecting a high statistical power to minimize the risk of Type *II* error.

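### The secondary mixed model starts from a random intercept plus an unstructured residual matrix, one covariance parameter too many, and fixes maximum likelihood where REML would give slightly better standard errors

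*Protocol article*

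**What the plan says.** Everything at issue stands in section 2.6 (Statistical analysis) of the protocol article, in the paragraph on secondary and longitudinal outcomes.

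- **Outcomes and visits.** Separate linear mixed models are planned for PSS-10, GAD-7, PHQ-9, PSQI and IES-R. The visits are given as "PSQI and IES-R scores across time points (Day 3, discharge, Day 30, Day 90", so there are four repeated measurements per person.
- **Fixed effects.** "Treatment group, time (as a categorical factor), the group × time interaction, and the corresponding baseline score of the outcome as a covariate". Baseline is therefore a covariate and not a fifth repeated measurement.
- **Random effects.** "A random intercept for each participant will be included to account for individual variability".
- **Residual covariance.** "An unstructured covariance matrix will be initially specified to model the within-subject errors, with the final structure chosen based on model fit indices", with AIC named as an example of such an index.
- **Estimation.** "For longitudinal LMMs, the full-information maximum likelihood (FIML) estimation inherent to the method will be utilized".
- **Status.** "All analyses of secondary outcomes and longitudinal trajectories are considered exploratory". Results are to be given as estimates with 95% confidence intervals, and p-values are to be read descriptively.

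The abstract gives the size: "This study will recruit 56 family members of ICU patients from a hospital in China". Section 2.1.2 derives this from 22 per group, raised to 28 per group for loss to follow-up.

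**The concern.** Two separate matters sit in this paragraph.

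The first is structural. A random intercept and an unstructured residual matrix both describe how measurements on one person correlate. Once the residual matrix is free in every element, nothing is left for the intercept variance to explain. The protocol attaches the unstructured matrix to the within-subject errors, so it cannot be read as the covariance of the random effects. The redundancy does not depend on sample size, and recruiting more people would not remove it.

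The second is the estimator. Maximum likelihood makes no allowance for the fixed effects it has estimated, so its variances are too small in small samples. REML makes that allowance, and it too uses all observed data under missing at random.

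At stake is the stability of the starting fit for all five secondary scales, the fairness of the AIC comparison, and the precision claimed by the confidence intervals through which the protocol intends these results to be read.

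**Working it through.** **Plan's own sample size.** Inputs from section 2.1.2: d = 1.13, two-sided alpha 0.05, power 0.95, equal groups. The noncentral t calculation gives 22 per group (power 0.956). Then 22/0.8 = 27.5, rounded up to 28 per group, or 56 in total. This agrees with the text. If 20% are lost, about 2 × 22 = 44 remain.

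**Parameter count.** Let V be the 4 × 4 marginal covariance of the four visits, τ² the intercept variance, J the matrix of ones and R the residual matrix. The model says V = τ²J + R.

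- Distinct elements of V: 4 × 5/2 = 10.
- Parameters: 10 in unstructured R plus 1 for τ² = 11.
- Rank of the derivative of V with respect to these parameters: 10.

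One parameter is redundant. Replacing τ² by τ² + c and R by R − cJ leaves V, and so the likelihood, unchanged. For example, take V with diagonal 1.0, 1.1, 1.2, 1.3 and all covariances 0.6. Intercept variances of 0, 0.2, 0.4 and 0.6 each leave a positive-definite R. At 0.6, R is diagonal with entries 0.4, 0.5, 0.6, 0.7. All four choices fit identically.

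**Other structures combined with a random intercept.**

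| Residual structure | Parameters | Rank |
|---|---|---|
| Identity | 2 | 2 |
| Diagonal | 5 | 5 |
| AR(1) | 3 | 3 |
| Compound symmetry | 3 | 2 |
| Toeplitz | 5 | 4 |
| Unstructured | 11 | 10 |

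**AIC.** The penalty is 2 per parameter. If the software counts all 11, the unstructured option is charged 22 instead of 20. Against identity, diagonal or AR(1) this is an unearned handicap of 2. Against compound symmetry or Toeplitz it cancels, because each of those also carries one redundant parameter.

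**Maximum likelihood against REML, by approximation.**

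- Group difference at a visit, with three between-person coefficients (intercept, group, baseline): variance ratio (N − 3)/N. At N = 56, 53/56 = 0.946, square root 0.973, so the SE is 2.7% too small. At N = 44, 41/44 = 0.932, square root 0.965, so 3.5%.
- Group × time contrasts, where the common baseline slope cancels for complete data: (N − 2)/N. At N = 56, 54/56 = 0.964, square root 0.982, so 1.8%. At N = 44, 42/44 = 0.955, square root 0.977, so 2.3%.

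**Maximum likelihood against REML, by simulation.** Assumptions: no treatment effect, unit variances, all correlations 0.5, unstructured V without a random intercept, interaction F-test with N − 2 denominator degrees of freedom, and losses unrelated to outcome. There were 12,000 to 15,000 runs per setting, so the Monte Carlo error of each rate is about 0.2 percentage points.

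| Setting | Day 90 SE, ML | Day 90 SE, REML | Ratio | Interaction type I error, ML | Interaction type I error, REML |
|---|---|---|---|---|---|
| N = 56, complete | 0.2261 | 0.2313 | 0.978 | 6.6% | 6.0% |
| N = 56, 20% lost by Day 90 | 0.2473 | 0.2539 | 0.974 | 6.8% | 6.0% |
| N = 44, complete | 0.2533 | 0.2608 | 0.971 | 6.7% | 5.8% |

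The Day 90 standard error is thus 2.2% to 2.9% too small under maximum likelihood. The reference distribution matters as well: with a chi-square in place of the F, the REML rates rise to 7.2–7.5%.

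**The case against.** The strongest reply is that the redundancy does not reach the planned inference. Only the split between intercept variance and residual covariance is undetermined. V, the fixed effects, the group × time test and the visit contrasts are all identified, and the protocol never proposes to report the intercept variance. This stands. A reader might infer that the model cannot be fitted or that the secondary results would be invalid; the document supports neither.

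A reader might also infer that convergence failures will decide the final structure. That is not shown. The unstructured matrix is only the starting point, and selection by fit index can lead to an identified structure such as a random intercept with identity, diagonal or AR(1) residuals. What remains is that the starting model is redundant as written, and the AIC count may be wrong by 2, which matters only in near-ties with those structures.

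On estimation, the sentence about maximum likelihood follows the text on multiple imputation, and its main purpose is to say how missing data are handled. That is fair, but it still names an estimator and calls it inherent to the method. Maximum likelihood is no obstacle to fitting: every simulated unstructured fit without the intercept gave usable estimates. Nor should the 2.7–3.5% shortfall for visit-level comparisons be carried over to the interaction, where the approximation gives about 2%. Part of the excess type I error remains under REML.

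Finally, a list of candidate structures and a fallback order may properly be left to an analysis plan that is not shown. Preferring a fallback triggered only by non-convergence over AIC would be a matter of taste, and it is not part of this point.

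**Conclusion.** The point holds in a limited form. The starting model has 11 covariance parameters for 10 moments. This follows from the text and needs no assumption beyond the four listed visits. Its practical cost is possible warnings or an unstable fit, and an AIC count up to 2 too high against identified structures if the software counts the redundant term.

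The choice of maximum likelihood is a separate and modest matter. Standard errors are roughly 2–3% too small, and interaction type I error is less than one percentage point higher than under REML. The simulated figures rest on the assumed correlation of 0.5, on losses unrelated to outcome, and on N between 44 and 56.

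The reach is confined to secondary analyses that the protocol calls exploratory. The primary comparison is an ANCOVA at Day 3 and does not depend on this model. The correction is still worth making, because it amends stated rules at almost no cost and slightly improves the intervals on which the secondary results will be judged.

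**What to change.** Amend the mixed-model description in section 2.6 in two places.

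1. **Covariance.** Specify an unstructured residual matrix over the four post-baseline visits with no random intercept (10 parameters for 10 moments). Alternatively, keep the random intercept and pair it with a simpler identified residual structure, such as identity, diagonal or AR(1). Compound symmetry and Toeplitz should not be combined with a random intercept. AIC may still be used among identified structures.
2. **Estimation.** Replace full-information maximum likelihood with REML and name a small-sample degrees-of-freedom method. Say that the likelihood-based analysis uses all observed data under missing at random, and drop the statement that maximum likelihood is inherent to mixed models.

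The cost is about two sentences of text. Design, sample size, data collection and the primary analysis do not change.

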#### Secondary outcomes

2.3.2

The secondary outcomes of this study focus on the trajectories of individual symptoms. To investigate the sustained and evolving effects of the intervention, individual scores for stress, anxiety, depression, PTSD, and sleep quality will be analyzed across a complete longitudinal time series. This series includes assessments at baseline (Day 1), immediately post-intervention (Day 3), within 24 h after the patient’s discharge from the ICU, and at the 30-day and 90-day follow-ups.

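### In the secondary mixed models, between-group comparisons at each visit depend on a group × time test that a sustained benefit cannot make significant beyond chance

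*Protocol article*

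**What the plan says.** All of this is in the Protocol article.

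- **Outcome rows of the models** (Statistical analysis, 2.6): scores "across time points (Day 3, discharge, Day 30, Day 90". Day 1 is not among them.
- **Fixed effects** (2.6): "Treatment group, time (as a categorical factor), the group × time interaction, and the corresponding baseline score of the outcome as a covariate".
- **Designated test** (2.6): "The group × time interaction will be the effect of primary interest, testing whether the change in the outcome over time differs between groups".
- **Gate** (2.6): "If the interaction is significant, simple effects analyses (e.g., between-group comparisons at each time point) will be conducted".
- **Objective for stress, anxiety and depression** (Study aims and hypotheses, 1.1): "examining its sustained effects at Day 3 post-enrollment (post-intervention), upon patient transfer from the ICU, and at the Day 30 and Day 90 follow-ups".
- **Hypotheses** (1.1): for PSS-10, GAD-7 and PHQ-9, "the intervention group will show greater reductions or faster improvement in individual scores", counted from baseline to each follow-up; for IES-R and PSQI, lower scores than in the control group.
- **Description of the series** (Secondary outcomes, 2.3.2): "This series includes assessments at baseline (Day 1), immediately post-intervention (Day 3", followed by the later visits. Here baseline belongs to the longitudinal series, whereas in 2.6 it is a covariate.
- **Status** (2.6, multiplicity paragraph): secondary and longitudinal analyses are exploratory, p-values are descriptive, and point estimates with 95% confidence intervals are promised. The paragraph does not say for which contrasts.

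**The concern.** What a group × time term tests depends on whether baseline is an outcome row or a covariate. The plan's explanation of the term, as a test of differing change over time, would cover change from baseline only if Day 1 were a level of time. With baseline on the right-hand side, the term compares the group difference at the four post-baseline visits with one another.

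Most of the secondary hypotheses in 1.1 concern the size of the group difference at a visit: a sustained effect, a greater reduction from baseline to each follow-up, lower IES-R and PSQI scores. The designated test does not address these, and the gate makes the contrasts that do address them depend on it. If the intervention works early and keeps working, the plan as written would usually yield a non-significant interaction and no between-group comparison by visit. The gap is widest for IES-R and PSQI, and for every visit after Day 3, because the primary analysis covers none of these.

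**Working it through.** **1. The plan's own figure.** Sample size (2.1.2) gives 22 per group for d = 1.13, two-sided α = 0.05 and power 0.95, and 28 after 20% loss. The normal approximation is n = 2(1.960 + 1.645)²/1.13² = 20.4, so 21; the noncentral t calculation gives 22; and 22/0.80 = 27.5, so 28. The figures reproduce. The plan states no power for the interaction test.

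**2. What the interaction tests.** For participant i at post-baseline visit t, with baseline score b and group indicator G, the model is

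Y(i,t) = μ(t) + β·b(i) + δ(t)·G(i) + u(i) + e(i,t), for t = Day 3, discharge, Day 30, Day 90.

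The group × time null hypothesis (3 df) is δ(Day 3) = δ(discharge) = δ(Day 30) = δ(Day 90). If all four equal the same δ, this null is exactly true and the rejection rate is α = 0.05 for any δ and any sample size. Were Day 1 a level of time, randomisation would give δ(Day 1) = 0, and a constant δ after it would violate the null. So the choice between covariate and outcome row decides whether the term responds to a sustained benefit.

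**3. Simulation.** 2,000 trials per scenario; baseline plus four visits; SD 1; equal correlation between all visits; complete data. The correlation is not in the documents, so 0.3, 0.5 and 0.7 were assumed. Interaction: the 3-df within-subject F test, which is the mixed-model test under equal correlation. Comparators: the baseline-adjusted group difference averaged over visits and at each visit. The pilot pattern uses the perceived-stress values in 2.1.2 (d = 1.50, 1.23 and 1.13 at Days 3, 30 and 90), read as group differences in SD units, with 1.50 assumed at discharge.

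Percentage of trials significant, 28 per group, range over the three correlations:

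| True effect at the four visits | Group × time | Average difference | Each visit |
|---|---|---|---|
| 0.5 constant | 5–6 | 84–92 | 48–73 |
| 0.7 constant | 4–5 | 98–99.8 | 74–95 |
| 1.13 constant | 4–5 | about 100 | 99–100 |
| Pilot: 1.50, 1.50, 1.23, 1.13 | 21–44 | about 100 | 99–100 |
| Strong fading: 0.7, 0.5, 0.3, 0.1 | 34–72 | 67–79 | 75–94 at Day 3, falling to 7 at Day 90 |

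The simulation error at 5% is √(0.05 × 0.95/2000) = 0.5 percentage points, so the first three rows agree with α. With 22 per group the interaction is again significant in 4–6% under a constant effect. A separate run with an unstructured covariance matrix (4,000 trials, 28 per group) gave 4.9% for the interaction against 99% for the average difference at d = 0.7 and correlation 0.6.

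**4. Whether other text fills the gap.** The additional analyses in 2.6 offer paired tests, which are within-group and do not compare the arms. The promise of estimates and intervals names no contrast.

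**The case against.** The case on the other side has several parts, and most of them limit the point without removing it.

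- **Exploratory status.** The secondary analyses are declared exploratory with descriptive p-values, so no formal claim depends on the interaction. The primary Day 3 composite comparison is an ungated, baseline-adjusted group contrast and is untouched. This stands and lowers the severity. It does not make the test answer the stated hypotheses.
- **The group difference is not lost.** A reader might infer that a sustained benefit would be invisible and that the visit comparisons would never be run. The text does not support this. Treatment group is a fixed effect in the same model, estimates with intervals are promised, and the comparisons do run whenever the interaction is significant. What remains is that 2.6 designates no group estimate other than the gated ones.
- **Group × time fits part of the question.** The objectives speak of trajectories and one hypothesis allows for faster improvement, which the term does address. So it would be wrong to infer that every secondary question could be reported as no effect. For stress, anxiety and depression, a Day 3 benefit is also sought by the primary composite.
- **The 5% is built in.** It is α under a true null, not a measured loss of power, and a perfectly constant effect is a limiting case. That is fair. The pilot's declining pattern is the better guide, and 21–44% is still low beside 99–100% for the contrasts being withheld.
- **A significant interaction may only reflect fading.** This is no harm in itself, because the gate then opens and the visit comparisons would show the fading.
- **Detail left to an analysis plan.** The article itself fixes the model, the test and the gate. The point concerns a stated rule, not an omission.

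**Conclusion.** The rule is wrong as written, with moderate severity. In the model that 2.6 specifies, group × time does not test whether change from baseline differs between groups, and making the visit comparisons conditional on it withholds the results that most of the secondary hypotheses call for. Under a benefit constant from Day 3 to Day 90 the gate stays shut in about 95% of trials; this follows from the model and needs no assumption about correlation or effect size. Under the pilot pattern it stays shut in about 56–79% (100 minus 44, and 100 minus 21). Those figures rest on 28 per group, complete data, equal correlations of 0.3–0.7, and an assumed discharge effect of 1.50.

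A reader might go further and treat this as a threat to the trial's main conclusion. The documents do not support that: the primary endpoint has its own analysis and the affected analyses are labelled exploratory.

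**What to change.** In 2.6, delete the condition that the interaction be significant. State that, for each secondary scale, the baseline-adjusted between-group difference with 95% CI at Day 3, discharge, Day 30 and Day 90 will be reported from the same mixed model whatever the interaction shows. The difference averaged over the four visits can be added as an optional summary. Keep group × time as the test of differing trajectories, which suits the faster-improvement hypothesis, and describe it as a test of whether the group difference varies among the post-baseline visits.

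Reconcile 2.3.2 with 2.6, so that both say whether baseline is a covariate or part of the outcome series.

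The cost is a few sentences: same data, same model, no change to sample size or visits. It should be done before the data are unblinded.
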